# A cluster randomised feasibility pilot trial evaluating involving community-dwelling older adults in activities in relation to meals in a rehabilitation program; recruitment, data collection and protocol

**DOI:** 10.1186/s40814-018-0323-3

**Published:** 2018-08-06

**Keywords:** Rehabilitation, Meals on wheels, Dwelling older adults, Activities of daily living, Community health care

## Abstract

**Background:**

Community-dwelling older adults receiving support at home such as meals-on-wheels may lose the ability to preserve social, cognitive, and functional abilities, when becoming accustomed to and dependent of community aged care. When still able to cook older adults often hold some control over the foods that are prepared and which they eat, and which helps to foster identity. The purpose of this study is to assess feasibility of outcome measurements and sample size when conducting a pilot cluster randomized trial to evaluate community-dwelling older adults being involved in activities in relation to meals in a rehabilitation program.

**Methods:**

This cluster randomized controlled study will consist of two clusters of a total of 5 community aged care areas; the intervention cluster, which hold 3 community aged care areas and the control cluster which hold 2 areas. The 130 community-dwelling older adults, receiving meals-on-wheels, will randomly be allocated to either the intervention cluster consisting of 8 weeks of participation in a rehabilitation program led by a Case Manager or the control cluster receiving usual community aged care. The primary outcome will be assessment of data collection (ratio between completed- and non-completed data) and assessment of sample size. The secondary clinical outcomes will be health-related quality of life (EQ-5D-3 L), muscle strength (chair stand), nutritional status (weight/BMI), loneliness (UCLA scale), mental well-being (Warwich-Edinburgh scale), self-efficacy (General Self-Efficacy scale), satisfaction with food-related life (SWFL scale) and refrigerator content.

**Discussion:**

This study evaluates community-dwelling older adults receiving support at home, using involvement in activities related to meals with a rehabilitation approach, and this is a new area of research and will therefore be contributing in developing and refining consistent practices of rehabilitation programs.

**Trial registration:**

ClinicalTrials.gov (registration no: NCT03289598). The protocol has been sent to the Danish Ethical Board which has concluded that approval is not needed and that the study can be carried on as described. Approval by The Danish Data Protection Agency has been giving through general approval for use of data in The City of Odense and will follow rules for obtaining the data accordingly.

## Background

Effective and good care to older adults in the community is necessary to prevent disease, to manage chronic illness, and to stay independent as long as possible. Alongside aging come special health challenges, such as dependency, limited mobility, frailty, and other physical or mental health problems. Systematic reviews and meta-analyses suggest that nutritional support may improve clinical outcome such as mortality and complication rates [1, 2]. Only few of the studies included have been performed among community-dwelling older people receiving support at home and the major focus has been on oral nutritional supplements. With the focus of care shifting from the hospital to the community malnutrition care is to become an important issue to address in the community [3].

Studies have found a high prevalence of undernutrition among older adults receiving support at home and that this increases the risk for dependency in activities of daily living and hence the need for care [4–7]. Older adults receiving community aged care have a significant improvement in quality of life having a higher proportion of individualized activities as a rehabilitation program [8]. Rehabilitation can be defined as a series of interventions that support the individual who is at risk of impaired functioning, in achieving and maintaining the best possible functioning, including working in conjunction with the surrounding community [9].

A recent review showed that case management in community aged care can improve client psychological health or well-being and unmet service needs [10]. In addition, there is recognition that a registered dietitian, particularly one trained in self-management education techniques, may be the health care professional best-suited to deliver nutritional intervention [11, 12]. The Danish Health Authority also recommend using Dietitians as Case Managers in rehabilitation processes, since it is beneficial to have a team of professionals that are interdisciplinary as Case Managers working with rehabilitation processes in the municipalities.

Three systematic reviews have looked at benefits achieved by means of meals-on-wheels offered to older adults [13–15]. Home-delivered meal programs improve diet quality and increase nutrient intakes among participants [13]. However, more research is needed to evaluate the efficacy and effectiveness of home-delivered meals for older adults on multiple outcomes [14]. Very few randomized controlled studies have assessed the beneficial effect of meals-on-wheels as a supportive intervention [15]. In addition, no randomized controlled intervention studies have been investigating rehabilitation related to limitations of “Activities of daily living” (ADL) e.g. cooking, has any beneficial effect [16].

Support at home such as meals-on-wheels means becoming accustomed to a new mealtime experience. E.g. when still able to cook older adults often hold some control over the foods that are prepared and which they eat, and which helps to foster identity. Foods prepared at home are familiar to the person, holding memories of the past and as well, the activities of grocery shopping, meal planning, and food preparation may help to preserve social, cognitive, and functional abilities.

In this pilot trial, the primary research aim is to explore the community-dwelling older adults acceptability and feasibility of the outcome measurements as methods to measure efficacy of the intervention, and to provide data to estimate the required sample size for a future cluster randomized study of community-dwelling older adults being involved in their own meals in a rehabilitation program.

The second aim of this study is to perform a pilot cluster randomized trial to understand, on an individual level, whether community-dwelling older adults receiving meals-on-wheels experience an improvement in health-related quality of life and muscle strength, being involved in their own meals in a rehabilitation program compared to usual community aged care including receiving meals-on-wheels.

The cluster design is chosen primarily to avoid contamination, since the assigned Health Care Staff and Registered Dieticians receiving additional training could not be expected to treat individual residents differently; respectively the intervention and the control group, by preference of the older person. Also, the cluster design is chosen due to practical reasons, in order not to conflict with other nutritional projects and initiatives in the participating municipality.

## Methods

This protocol follows both the CONSORT 2010 statements extension for the reporting of cluster randomized trials [17] and the CONSORT 2010 statements extension to randomized pilot and feasibility trials [18], along with the SPIRIT 2013 guideline and checklist recommended for clinical trial protocols [19].

### Trial design

This study is a cluster randomized trial where clusters are a total of five community aged care areas in The City of Odense allocated into groups of two clusters. The two clusters are 1) the group of older adults being involved in own meals in a rehabilitation program (Intervention) (*n* = 3) and 2) usual care (Control) (*n* = 2). In the City of Odense there are 33,800 citizens above 65 years of age, and totally residents receiving support at home are 5453 (18+ years of age). 1477 citizens (18+ years of age) are receiving meals-on-wheels.

The intervention in the study consists of two parts (see below) targeted at individual participant level, and to separately investigate the two parts of the intervention a pre- and post-intervention comparison will be made.

An overview of the trial is presented in Fig. 1 Design of the study and flow of participant.

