The first part, will consist of education of Health Care Staff in the intervention cluster starts immediately after finishing the baseline assessments and consists of a total of one day of education divided into three days, focusing of aspects of food, meals and nutrition to older adults. The education is performed by Bachelor’s Degree Nutritional and Health Educated Professionals that work within The City of Odense. Also included in the first part of the intervention, training of the Care Manager/RDs including learning to use the new developed tool was performed. The Case Managers will be Registered Dieticians (RDs) and will before commencement of the intervention be trained in managing a rehabilitation program focusing on meals. The training will consist of three days. One day as follow-up on the rehabilitation program. Specific topics include; assessment of functional abilities in relation to meals; goal setting by means of Goal Attainment Scaling (GAS) [24], ethical considerations and communication. The training program is developed specifically for the present study in co-operation with teachers from The University of Southern Denmark (SDU) - Master in Rehabilitation.

The effect of the education and training is assessed due to outcomes on an individual level (see below).Second part of the intervention - Rehabilitation program

In the second part of the intervention, the individual participants in the intervention cluster, will be participating in a rehabilitation program involving collaborative goal setting with a Case Manager.

Before contacting the individual participant, the Case Manager/RD will make a review of the participant’s journal in the municipalities system to find out 1) what kind of food from the meals-on-wheels is delivered, 2) if the participant presently is involved in other rehabilitation programs within the municipality, 3) the present health care situation of the participant, and 4) if the participant formerly had any visit from a RD in the municipality. These data will only be used for the rehabilitation program by the Case Manager/RD that is visiting the participant and will not be systematic collected and registered.

The *assessment* will help the participant and the Case Manager/RD to make collaborative evidence-based *goalsetting* to select initial areas for chance of meal activities.

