### Outcomes

The outcome assessments, conducted in the participants homes by Research Assistants (RA) and Case Managers/RD’s will occur at inclusion (Baseline, *t* = 0) and at the end of the intervention period (Follow-up, *t* = 2). At the beginning of second part of the intervention some outcome assessments will also be conducted in only the Intervention cluster (In between, *t* = 1). It is, however, not obtained by the same person at baseline, in between, and follow-up for practical reasons. However, all will receive the same training in the methods on obtaining outcome assessments by RA ([name]) or RA ([name]). Due to the design of the study it is not possible to blind neither the RA’s nor the Case Managers/RD’s. An overview of the outcome measurements is presented in Table 1 and described in detail below.

**Table 1 Tab1:** Data collection 2 Content in fridge (sufficient, insufficient, empty)

Measure	Time of data collection		
	Baseline *T* = 0	In between *T* = 1	Follow-up *T* = 2
Quality of life by EQ-5D-3 L	X	X	X
Height, meter	X	X	X
Weight, kg	X	X	X
BMI, (kg*kg/m2)	X	X	X
Muscle strength - Chair stand^1^	X	X	X
Satisfaction with food-related life	X	X	X
UCLA Loneliness Scale	X		X
The Short Warwich-Edinburgh Mental Well-being Scale	X		X
General Self Efficacy Scale	X		X
Refrigerator content^2^	X		X
Sociodemographic	X		
Meals-on-wheels (days/w)	X		

^1^Rise from a chair without using the arms in 30 s

^2^Content in fridge (sufficient, insufficient, empty)

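### The plan promises separate effects for staff education (part 1) and rehabilitation (part 2), but the in-between visit exists only in the intervention arm, so only the combined package has a controlled comparison

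*Protocol article*

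**What the plan says.** All references are to the protocol article.

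- **Trial design** describes an intervention in two parts and states that "to separately investigate the two parts of the intervention a pre- and post-intervention comparison will be made".
- **Preparation of the intervention** covers part 1, the education of health care staff and the training of Case Managers. It states that "The effect of the education and training is assessed due to outcomes on an individual level". On timing, "education of Health Care Staff in the intervention cluster starts immediately after finishing the baseline assessments".
- **Outcomes** sets the schedule. Both arms are assessed at baseline (t=0) and follow-up (t=2). For t=1: "At the beginning of second part of the intervention some outcome assessments will also be conducted in only the Intervention cluster".
- **Table 1** has t=1 entries for EQ-5D-3L, height, weight, BMI, chair stand and satisfaction with food-related life. It has none for UCLA loneliness, SWEMWBS, General Self-Efficacy or refrigerator content.
- **Outcomes** also says that assessments are "conducted in the participants homes by Research Assistants (RA) and Case Managers", and that they are "not obtained by the same person at baseline, in between, and follow-up for practical reasons". Neither group of assessors is blinded. The stated safeguard is that "all will receive the same training in the methods on obtaining outcome assessments".
- **Analysis** plans tests of change within and between groups, and a model with cluster as a random effect.

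**The concern.** A before-after change in one arm measures the effect of a component only if nothing else would have moved the outcome over that interval. In older people receiving home support that cannot be taken for granted, and the control arm is there to remove such movement. Here the control arm is not observed at the point where part 1 ends and part 2 begins, so it can correct the total change but neither piece of it.

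At stake is what the pilot may say about its components. The Conclusions section says that the pilot results will be used to design the definitive trial. If a within-arm change were read as the effect of education, or of rehabilitation, that reading could influence which component is carried forward.

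**Working it through.** **1. What is observed.** The schedule yields five arm-by-time means: intervention I0, I1, I2 and control C0, C2. There is no C1.

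**2. What each contrast contains.** Let E1 be the effect of part 1 seen by t=1, L1 any effect of part 1 that appears only after t=1, and E2 the effect of part 2 given part 1. Let D01 and D12 be the non-treatment change over each interval (time, regression to the mean, repeat testing, assessor differences).

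- I1 − I0 = E1 + D01
- I2 − I1 = E2 + L1 + D12
- C2 − C0 = D01 + D12, if the arms share the same non-treatment change
- (I2 − I0) − (C2 − C0) = E1 + L1 + E2

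The last line is the combined package, and it can be formed. E1 on its own needs D01, and E2 + L1 needs D12. Only the sum D01 + D12 is available from controls.

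L1 is a real possibility. Part 1 includes the training of Case Managers, who work with participants in part 2, so an effect of that training would be expected after t=1.

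**3. The split is undetermined: an invented example.** Suppose the intervention arm changes by +0.05 in each interval and the control arm by +0.05 in total.

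- If all the control change falls after t=1 (D01 = 0, D12 = 0.05): E1 = 0.05 − 0 = 0.05, and E2 + L1 = 0.05 − 0.05 = 0.
- If it all falls before t=1 (D01 = 0.05, D12 = 0): E1 = 0.05 − 0.05 = 0, and E2 + L1 = 0.05 − 0 = 0.05.

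The combined effect is 0.10 − 0.05 = 0.05 either way. The same data fit opposite conclusions about the two parts, and no analysis method can choose between them without a control value at t=1.

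**4. Outcomes without t=1.** For UCLA, SWEMWBS, self-efficacy and refrigerator content, I1 is also missing, so not even the within-arm pieces exist.

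**5. Illustration of consequence.** The document gives no figure for D01 or D12, so their sizes are assumed.

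Inputs from Sample size: n = 53 in the arm; EQ-5D SDs 0.222 and 0.355 from the earlier study, pooled as √((0.222² + 0.355²)/2) = 0.296. Assumed: the same SD at both visits, within-person correlation ρ of 0.5 or 0.7, true part effect zero, two-sided 5% paired test, normal approximation.

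SE = 0.296 × √(2(1 − ρ)) / √53; λ = drift / SE; rejection rate = Φ(λ − 1.96) + Φ(−λ − 1.96).

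For drift 0.05 and ρ = 0.5: SE = 0.0407, λ = 1.23, rate 23.3%.

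| Assumed drift | ρ = 0.5 | ρ = 0.7 |
|---|---|---|
| 0 | 5.0% | 5.0% |
| 0.03 | 11.4% | 15.9% |
| 0.05 | 23.3% | 35.5% |
| 0.08 | 50.3% | 71.9% |
| 0.10 | 69.1% | 88.8% |

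The table shows how a within-arm test behaves under drift. It does not estimate the drift in this trial.

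**The case against.** The strongest reply is that separating the parts belongs to neither stated aim. The aims in Background are feasibility with sample size and, second, the programme against usual care. Trial design openly calls the split a pre-post comparison and does not present it as controlled. Both outcomes named in the second aim, EQ-5D-3L and chair stand, are measured at t=1. This stands as a limit on weight. It does not remove the point, because the text still claims to investigate the parts separately and to assess the effect of one of them. An unseen analysis plan could not help, since the missing item is data that the schedule does not collect.

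A reader might infer more than the document supports:

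- **That change of assessor by itself destroys identification.** It does not. It adds possible measurement bias, which common training partly addresses. The decisive gap is the absent control visit.
- **That Case Managers score the follow-up of their own programme.** They are named among the assessors, but the article does not say who does which visit, so no reassignment of t=2 visits can be argued from it.
- **That the four instruments without t=1 contradict the text.** They do not. Outcomes says that only some assessments are made then, and Table 1 agrees.
- **That any t=0 to t=1 change will be reported as an education effect.** No reporting rule says so. The wording invites that reading but does not fix it.
- **That the combined effect is also unidentified.** It keeps a control comparison, although the Randomization sections (allocation by organisational turn, intervention arm recruited first) give other reasons for caution.

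**Conclusion.** The point holds for the part-specific effects and is wrong as written: the design cannot deliver a separate effect of education or of rehabilitation. This rests on the stated schedule alone and needs no numerical assumption. The t=0 to t=2 between-arm contrast for the whole package is the only one with a control comparison, and reading it as an effect assumes that non-treatment change is alike in the two arms.

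The magnitude of bias in the within-arm changes is unknown. The rejection rates above depend on assumed drifts and correlations. Because the split lies outside both stated aims, the matter is one of limiting what may be concluded and does not undermine the pilot as a whole.

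**What to change.** 1. In Trial design and in the description of part 1, state that the only comparative estimate is the t=0 to t=2 contrast between arms for the combined package.
2. Report the intervention-arm changes from t=0 to t=1 and from t=1 to t=2 as exploratory and descriptive (mean change with 95% CI), without attributing them to education or rehabilitation.
3. Delete or reword the sentence saying that the effect of education and training is assessed.
4. Note that UCLA, SWEMWBS, self-efficacy and refrigerator content have no t=1 value, so only the t=0 to t=2 change is available for them.

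The cost is wording, with no added visits or data. The downside is that the plan gives up its part-specific effect claim. Keeping that claim would require a matching t=1 assessment in controls, which means extra home visits in a study that describes its funding as limited. Even then, the second interval would show part 2 given part 1, together with any delayed effect of part 1.

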**Fig. 1 Fig1:**
[figure not shown]
Design of the study and flow of participant

### Participants

This study will use two sets of eligibility criteria, respectively for the community aged care areas (clusters) and the individual participants.

Community aged care groups (clusters): The citizens who need health care in The City of Odense are placed in a total of five community aged care areas. Excepted are those suffering from severe dementia, brain injury and mental illness, who receive special health care treatment outside the community aged care areas. All five community aged care areas will randomly be assigned into two clusters. The Intervention cluster consists of three community aged care areas: Dalum, Tagtaekker, and Skibhus, and the Control cluster consist of two community aged care areas: Rugaard, and Munkebjerg.

Inclusion and exclusion criteria for the individual participants:Inclusion criteriaCommunity-dwelling older adults (65+ years of age)Receiving meals-on-wheels (at least one time per/week) from the municipal supplier at the time of recruitmentLive in The City of OdenseExclusion criteriaModerate/severe dementia assessed by the community Health Care StaffBeing deaf and/or not understand the language of DanishNot being able to sign the informed consentReceiving (or likely to receive in the next 6 months) enteral tube feeding or parenteral nutrition;Participating in other project in the municipality about nutritional support in the form of dietetic adviceReceiving meals-on-wheels from a private supplier at the time of recruitmentOn an end-of-life care pathway

The reason for exclusion of older adults being deaf or not speaking Danish language is that the project has limited funding for translation into different languages, and it will not be possible to hire a deaf interpreter. It is, however, estimated by the researchers involved, that only a few will be excluded due to this reason.

### Intervention

The entire intervention, including the phase of preparation is showed in Fig. 2 Flow of intervention, including preparation of the intervention.

**Fig. 2 Fig2:**
[figure not shown]
Flow of intervention, including preparation of the intervention

In Denmark a rehabilitation process is described as short, time-bound, organized, and conducted in a holistic and interdisciplinary manner. The rehabilitation process should be built around individual goals in cooperation with the individual recipient and the professionals [20]. A rehabilitation process consists of several phases; *allocation*, *assessment*, *goalsetting*, *care planning* and *implementation*, *monitoring* and *reassessment* [10, 21]. The rehabilitation program in this study will be going through all phases of the participant’s rehabilitation after *allocated* to the study.

#### Preparation of the intervention

Based on a systematic literature research and a workshop for experts and representatives of the older adults in Denmark, a tool to be used in the rehabilitation process and the dialog between the Case Manager/RD and the older adults was developed. This tool will be new and is not a validated standardized tool. Both Goal Attainment Scaling (GAS) and “A common terminology for community aged care in Denmark” (FSIII) will be used in this tool. GAS offers many potential advantages as an outcome measure for rehabilitation, and moreover there is also evidence that GAS has positive therapeutic value in encouraging the participants to reach their goals [22]. FSIII is a generic process model using the same concept and the same way of describing the reasons for care planning and interventions in rehabilitation programs in order to efficiency improvement of the communication [23]. The tool includes the following focusses of meals:manage shopping (i.e. help to plan the shopping, grocery shopping),increase cooking abilities (e.g. semi-prepared meals-on-wheels, assistance to cook at home),focus on social aspects of meals (e.g. eating together with family, buddies/volunteers), andimprove ability to eat independently (e.g. in relation to dysphagia).

The intervention consists of two parts targeted at individual participant level:First part of the intervention: Education and training

The first part, will consist of education of Health Care Staff in the intervention cluster starts immediately after finishing the baseline assessments and consists of a total of one day of education divided into three days, focusing of aspects of food, meals and nutrition to older adults. The education is performed by Bachelor’s Degree Nutritional and Health Educated Professionals that work within The City of Odense. Also included in the first part of the intervention, training of the Care Manager/RDs including learning to use the new developed tool was performed. The Case Managers will be Registered Dieticians (RDs) and will before commencement of the intervention be trained in managing a rehabilitation program focusing on meals. The training will consist of three days. One day as follow-up on the rehabilitation program. Specific topics include; assessment of functional abilities in relation to meals; goal setting by means of Goal Attainment Scaling (GAS) [24], ethical considerations and communication. The training program is developed specifically for the present study in co-operation with teachers from The University of Southern Denmark (SDU) - Master in Rehabilitation.

The effect of the education and training is assessed due to outcomes on an individual level (see below).Second part of the intervention - Rehabilitation program

In the second part of the intervention, the individual participants in the intervention cluster, will be participating in a rehabilitation program involving collaborative goal setting with a Case Manager.

Before contacting the individual participant, the Case Manager/RD will make a review of the participant’s journal in the municipalities system to find out 1) what kind of food from the meals-on-wheels is delivered, 2) if the participant presently is involved in other rehabilitation programs within the municipality, 3) the present health care situation of the participant, and 4) if the participant formerly had any visit from a RD in the municipality. These data will only be used for the rehabilitation program by the Case Manager/RD that is visiting the participant and will not be systematic collected and registered.

The *assessment* will help the participant and the Case Manager/RD to make collaborative evidence-based *goalsetting* to select initial areas for chance of meal activities.

In the present study, goals will be short-term (i.e. realistic to reach within the intervention period), and a maximum of three goals will be selected for change.

Thus, the Case Managers will encourage participants to involve in these activities.

When *implementing* the activities in relation to meals the Care Manager/RD will plan the intervention interdisciplinary with other professionals within The City of Odense e.g. Occupational Therapist, Physiotherapist, Health Care and Kitchen Staff. A period of eight weeks is chosen for the rehabilitation program in order to get a realistic comparison. This is the minimum amount of time for a Danish municipality rehabilitation program [21]. The intervention is individual and will consist of a minimum of three contacts to the Case Manager/RD in order to *monitor* and *reassess*. After completion of the rehabilitations program a final evaluation will be made.

The participants in the control group will receive usual care in relation to meals; this includes a number (one to seven) hot meals-on-wheels arriving one to three times per week, along with usual support at home.

